### Recruitment {15}

The recruitment process will focus on the Lithuanian-speaking population and will utilize various methods to ensure sufficient participant enrollment. Announcements about the study will be made at tinnitus and hearing-related support groups, audiology organizations, and their newsletters and hearing clinics, as well as audiology departments and through social media. Interested individuals will be able to access information and register for the study through the study website.

### Assignment of interventions: allocation

#### Sequence generation {16a}

The principal investigator (PI) will utilize a random number generator (random.org) to allocate all participants randomly and equally to the study groups without stratification.

#### Implementation {16c}

Once the recruitment is complete, a principal investigator of the study will generate an allocation sequence using a random list generator www.random.org. The list will contain the number of items corresponding to the size of recruited participants. For example, if 60 participants will be recruited, then a list with 60 letters (20 letters a (a = treatment group no 1), 20 letters b (b = treatment group 2), and 20 letters c (c = waiting list control) arranged in a random order will be produced. This list will be added side-by-side to a list of alphabetically arranged codes (no personal information) generated to each participant upon registration.

### Assignment of interventions: blinding

#### Who will be blinded {17a}

Because of the psychological nature of the intervention, it is not possible to maintain blinding for either the participants or the study team members following the assignment to their respective intervention groups. All outcomes will be assessed via self-report measures which eliminate assessor bias. Data analysts will not be blinded because data output will be generated automatically from the study platform and will contain information specific to different study groups (completed modules, etc.) and will allow identification of assigned groups.

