### Trial design {8}

This study is three-armed parallel-group randomized controlled non-inferiority trial. Participants will be randomized to all groups equally.

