### Sample size {14}

In order to attain 80% power with a 5% alpha level, a three-means non-inferiority test (ANOVA) was performed, resulting in a required sample size of 42 participants in total. To account for potential dropouts, the number of participants was increased by 25%, resulting in approximately 18 participants per study arm. This dropout rate is common for therapist-guided internet-based interventions. The primary end point used for the non-inferiority test was the THI score at 8 weeks, and the equivalence margin was determined to be 7 points, based on the mean minimally clinically important difference (MCID) found in a prior study [47].

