#### Confidentiality {27}

After giving informed consent, potential and enrolled participants will be asked to provide their email addresses and telephone numbers. The platform generates a unique code for each registered individual and stores it on a secure server available only to the research team with administrative rights after logging. Only non-personal data will be available from the data repository after the trial.

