## Statistical methods

### Statistical methods for primary and secondary outcomes {20a}

The differences between the groups at baseline will be evaluated using independent samples *t*-tests for continuous variables and chi-square tests for categorical variables or their non-parametrical equivalents. In order to assess the potential changes in the primary and secondary outcomes and compare them between the intervention groups and the control group, repeated-measures ANOVAs will be performed. The results from all baseline assessment measures will be utilized as predictors. The study will calculate both within-group and between-group effect sizes. The between-group effect sizes will be determined by calculating the mean difference from the pre-test to the post-test for short-term effects and from the pre-test to follow-up for long-term effects, using the standard deviations of each group at the pre-test. The within-group effect sizes will be calculated using the means and standard deviations at all time points for every group. We will use regression analysis to investigate the association between baseline variables and outcome measures, with the goal of identifying predictors of the outcome.

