### Methods in analysis to handle protocol non-adherence and any statistical methods to handle missing data {20c}

The results will be calculated based on the per-protocol approach and will also be compared with those obtained using the intention-to-treat approach. To perform the intention-to-treat analysis, a missing value analysis will be carried out. If necessary, missing data will be filled in using multiple imputation techniques.

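### The data-export reason given for unblinded analysts does not prevent masking the ICBT versus iMBTSR comparison of week-8 THI

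*Protocol article*

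**What the plan says.** - **Analysts.** Section {17a}: "Data analysts will not be blinded because data output will be generated automatically from the study platform and will contain information specific to different study" arms. The only field named is module completion: "completed modules, etc.) and will allow identification of assigned groups".
- **Everyone else.** The same section says "it is not possible to maintain blinding for either the participants or the study team members following the assignment". It adds that self-report removes assessor bias.
- **Design and endpoint.** Section {8}: "This study is three-armed parallel-group randomized controlled non-inferiority trial". Section {14}: "The primary end point used for the non-inferiority test was the THI score at 8 weeks", with a margin of 7 points.
- **Analysis sets and missing data.** Section {20c} bases results on the per-protocol approach and compares them with intention-to-treat. After a missing value analysis, "If necessary, missing data will be filled in using multiple imputation techniques".
- **Identifiers and allocation.** Section {27}: "The platform generates a unique code for each registered individual". Section {16c} allocates by setting a random list of the letters a, b and c beside those codes.

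**The concern.** Participants and therapists cannot be blinded to a psychological treatment, so the analysis is the one stage of this trial that could still be masked. The protocol gives that up for a reason about the content of an automatic export. The remark that self-report removes assessor bias concerns how scores are collected, not what is done with them afterwards.

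In a non-inferiority trial, decisions on who counts as per protocol and whether to impute can move the estimate towards or away from the margin. A person who takes them knowing which arm is iMBTSR can favour the new treatment without intending to. Even if no one does, a reader of the results cannot rule it out.

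**Working it through.** **1. Does the stated reason prevent masking?** I set what the active-arm comparison needs beside what the protocol says reveals the arm.

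| Needed for week-8 THI, ICBT v iMBTSR | Does it reveal the arm? |
|---|---|
| Participant code ({27}) | No; generated at registration |
| Arm label ({16c}) | Not if the letters are recoded |
| Baseline and week-8 THI (Primary outcome measures; Table 1) | Not by format; same 25-item scale in both arms |
| Per-protocol membership ({20c}) | Not as a yes/no flag; yes if derived from raw module data |
| Module completion, platform use ({17a}) | Yes, but not an input to the THI comparison itself |

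Only the last row is arm-specific, and it enters only through the per-protocol flag. Deleting columns is therefore not enough by itself: someone who knows the arms must first turn module data into the flag.

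**2. How much could open choices matter?** No figure in the protocol depends on this point, so what follows is illustrative.

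Inputs from section {14}: margin 7, alpha 5% (sidedness not stated; one-sided assumed), 25% dropout, about 18 per arm. The arm size follows from the plan's own step: 42 × 1.25 = 52.5, and 52.5 / 3 = 17.5, rounded to 18.

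Assumed, because not stated: THI SD 20, pre-post correlation 0.6, and 80% of observed participants per protocol, with dropout and non-adherence at random.

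Expected numbers per arm: observed 18 × 0.75 = 13.5; per protocol 13.5 × 0.80 = 10.8.

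The true deficit is set equal to the margin, so every declaration of non-inferiority is an error. The test is a one-sided t-test of change in THI, shifted by 7.

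| Rule | False non-inferiority (6,000 trials) |
|---|---|
| Per-protocol set, fixed | 4.5% |
| Observed set, fixed | 4.8% |
| More favourable of the two | 6.3% |
| Both required | 3.0% |

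The Monte Carlo standard error on 6.3% is √(0.063 × 0.937 / 6000) = 0.3 points. Other runs of the two-set choice gave 7.1% for the change score and 7.0 to 7.5% with baseline adjustment, the latter over SD 10 or 20, correlation 0.5 to 0.7 and adherence 70 to 80%.

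**3. Check by formula.** The per-protocol set is a random fraction a of the observed set, so the two test statistics correlate at about √a. With each test at 5%, P(either) = 0.05 + 0.05 − P(both).
- a = 0.80: correlation 0.894, P(both) = 0.031, P(either) = 0.069.
- a = 0.70: correlation 0.837, P(both) = 0.027, P(either) = 0.073.

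This agrees with the simulations. The SD drops out because the shift by 7 removes the true difference, so the assumed SD does not drive the result.

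**The case against.** **Pre-specification, not masking, is the active ingredient.** An analyst who knows the arms but runs one fixed analysis stays at about 5%. This stands: the calculation bounds what free choice of analysis set could do and does not measure unblinding. Section {20c} also has the two results compared rather than one picked, and requiring both would bring the error down to about 3%.

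**An analysis plan that is not shown may fix the per-protocol rule and the imputation trigger.** This also stands, and their absence from the article is not the point here. {17a} is a stated choice with a stated reason, and rules set elsewhere would not change who sees the arms.

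**A reader might infer that the analyst may also choose between parametric and rank tests of the outcome, with larger inflation.** The documents do not support that. The words "chi-square tests for categorical variables or their non-parametrical equivalents" belong to the sentence on baseline differences. For the outcomes, section {20a} names repeated-measures ANOVA. An inflation figure that includes a rank test of THI would describe an option the plan never offers.

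**Masking would be incomplete.** Partly right. The waiting list completes no modules and chooses an intervention after week 8, so it may be guessable. The mindfulness scale (MAAS) could hint at the iMBTSR arm if supplied in the same file. Neither prevents masking the two active arms for the THI comparison.

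**Staffing.** The article does not say whether the analyst is separate from the core team, and the principal investigator generates the allocation. The remedy works only if a second person analyses.

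**Conclusion.** The point holds in a limited form. The reason in {17a} describes the export and does not justify leaving the analyst unblinded for the ICBT versus iMBTSR comparison of week-8 THI. Nothing in the protocol is false or contradictory here. It is an avoidable weakness in a stated choice, cheap to remove, and worth removing because no other stage of the trial can be masked.

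The size is small: from about 5% to about 6 to 7.5% false non-inferiority if the more favourable of two analysis sets were always taken. This assumes a one-sided 5% test, 70 to 80% adherence among those observed, and random dropout and non-adherence. Neither imputation nor the choice of per-protocol rule was simulated. A reader might take the figure as the bias caused by unblinding, or as a suggestion that results would be steered; the documents support neither.

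**What to change.** Replace the sentence on data analysts in {17a} with a procedure along these lines:

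1. A team member who holds the allocation list prepares the analysis file: participant code, masked arm labels, baseline and week-8 scores, and a yes/no per-protocol flag set by a rule fixed before export. Module and platform-use fields are left out.
2. An analyst who does not hold the list settles the imputation decision and runs the week-8 THI comparison on that file.
3. Labels are revealed once those results are locked, and engagement data are merged afterwards.

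If no second person is available, {17a} should say so, since that would be a genuine reason where the export format is not.

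Cost: one recoded export and a wording change. Downsides: engagement analyses wait until unmasking, the waiting-list arm may still be guessable, and the analyst must be someone other than the allocation holder.

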#### Procedure for unblinding if needed {17b}

The design is open label so unblinding will not occur.

### Data collection and management

#### Plans for assessment and collection of outcomes {18a}

Data will be collected at pre-randomization, termination, and 3- and 12-month follow-ups. All questionnaires will be self-report and administered online. To ensure that collected data is complete and accurate, the online questionnaires will be coded in a way that requires participants to fully answer the questions in order to submit the answers. For a full timeline of questionnaire dissemination, see Table 1.

#### Plans to promote participant retention and complete follow-up {18b}

All participants will be informed in the informed consent about follow-up assessments. If participants discontinue or deviate from intervention protocols, they will be contacted and study team members will first try to address any concerns participants might have that are altering their adherence to the intervention protocols. In case these concerns cannot be resolved, participants will then be asked to fill in follow-up self-assessment questionnaires online.

#### Data management {19}

Most of the data gathered online and saved to a database will be coded automatically. Only a small fraction of demographic data will need to be coded. Data will be stored on a secure server and, after the termination of the study, uploaded to MIDAS, a secure national scientific data repository, where it will be available upon request to the corresponding author after reports are published.

#### Confidentiality {27}

After giving informed consent, potential and enrolled participants will be asked to provide their email addresses and telephone numbers. The platform generates a unique code for each registered individual and stores it on a secure server available only to the research team with administrative rights after logging. Only non-personal data will be available from the data repository after the trial.

#### Plans for collection, laboratory evaluation, and storage of biological specimens for genetic or molecular analysis in this trial/future use {33}

Not applicable, no samples were collected.

## Statistical methods

### Statistical methods for primary and secondary outcomes {20a}

The differences between the groups at baseline will be evaluated using independent samples *t*-tests for continuous variables and chi-square tests for categorical variables or their non-parametrical equivalents. In order to assess the potential changes in the primary and secondary outcomes and compare them between the intervention groups and the control group, repeated-measures ANOVAs will be performed. The results from all baseline assessment measures will be utilized as predictors. The study will calculate both within-group and between-group effect sizes. The between-group effect sizes will be determined by calculating the mean difference from the pre-test to the post-test for short-term effects and from the pre-test to follow-up for long-term effects, using the standard deviations of each group at the pre-test. The within-group effect sizes will be calculated using the means and standard deviations at all time points for every group. We will use regression analysis to investigate the association between baseline variables and outcome measures, with the goal of identifying predictors of the outcome.

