**Discussion:**

Internet-delivered interventions offer a range of benefits for delivering evidence-based treatments. This is the first randomized controlled trial to directly compare Internet-delivered CBT and MBTSR for tinnitus in a non-inferiority trial.

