#### Primary outcome measures

To assess the impact of tinnitus on daily life, the Tinnitus Handicap Inventory (THI) will be used [37]. Assessment with THI will take place at pre-treatment, post-treatment at week 8, and 3 and 12 months post-treatment follow-ups. Change in the score from baseline will be assessed. The THI is designed to assess the impact of tinnitus on daily life and measures tinnitus-related functional limitations and emotional and catastrophic reactions. It is also widely used in research studies to measure the change in the severity of a tinnitus handicap before and after an intervention and therefore was selected as the primary measure of the study. The THI questionnaire consists of 25 questions. Answers are scored as follows: “yes,” 4 points; “no,” 0 points; and “sometimes,” 2 points. The total score is obtained by summing the scores of all 25 questions. A higher score indicates a higher disability caused by tinnitus and a higher impact of tinnitus on a person’s daily life. A validated Lithuanian language version of THI will be used in the study [38].

Weekly monitoring of changes in tinnitus handicap severity will be done using the Tinnitus Handicap Inventory Screening version (THI-S) [39]. A screening version of THI has 10 items from the original THI and will let assess the changes throughout the duration of the program. Assessment with THI-S will be done at weeks 2, 4, and 6.

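### The stated primary analysis, repeated-measures ANOVA, tests for no difference and never applies the 7-point margin, so it does not answer the declared non-inferiority question

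*Protocol article*

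**What the plan says.** Three places in the protocol article set the framework.

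- Trial design {8}: "This study is three-armed parallel-group randomized controlled non-inferiority trial".
- Abstract, Discussion, which names the pair of arms: "This is the first randomized controlled trial to directly compare Internet-delivered CBT and MBTSR for tinnitus in a non-inferiority trial".
- Sample size {14}: "In order to attain 80% power with a 5% alpha level, a three-means non-inferiority test (ANOVA) was performed", and "The primary end point used for the non-inferiority test was the THI score at 8 weeks". The margin given there is 7 THI points, taken from a published minimal clinically important difference.

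The analysis section, Statistical methods {20a}, says that to assess changes in the primary and secondary outcomes and "compare them between the intervention groups and the control group, repeated-measures ANOVAs will be performed". Baseline measures enter as predictors. Within-group and between-group effect sizes will also be calculated, from pre-test to post-test and from pre-test to follow-up. Section {20c} plans a per-protocol analysis and compares it with intention-to-treat. Neither section mentions non-inferiority, the margin, a confidence interval for iMBTSR against ICBT, or week 8 as the time of decision.

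**The concern.** A non-inferiority trial has to reject the hypothesis that the new treatment is worse than the reference by at least the margin. An ANOVA F-test has the opposite starting point, because its null is that the means do not differ. With a waiting-list arm among the three groups, a significant F may only show that treatment beats waiting. A non-significant F may only show that the trial is small. Neither outcome says whether iMBTSR is less than 7 points worse than ICBT.

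At stake is the trial's headline conclusion. As written, the plan contains no step by which non-inferiority could be concluded or rejected.

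**Working it through.** **1. What is fixed and what is analysed**

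| Element | Sample size {14} and design sections | Statistical methods {20a} |
|---|---|---|
| Question | Non-inferiority | Differences between arms |
| Comparison | ICBT with iMBTSR | Intervention groups and control group |
| Time | Week 8 | Occasions in the ANOVA not stated |
| Margin | 7 points | Not used |
| Decision rule | Not given | Not given |

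The pre-to-post effect size in {20a} does isolate week 8, but it is standardised and is never set against 7 points.

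**2. The plan's own figure**

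The plan states "resulting in a required sample size of 42 participants in total", which is 42/3 = 14 per arm. Then "the number of participants was increased by 25%, resulting in approximately 18 participants per study arm": 42 × 1.25 = 52.5, and 52.5/3 = 17.5, rounded to 18. The inflation step reproduces. The 42 cannot be reproduced, because no SD is stated. For a two-arm non-inferiority test with true difference 0, the SD that gives 14 per arm is

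SD = 7 × √(14/2) / (z₁₋α + z₀.₈₀)

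- one-sided 5%: 18.52/(1.645 + 0.842) = 7.4
- one-sided 2.5%: 18.52/(1.960 + 0.842) = 6.6

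**3. Illustration: a non-significant pairwise test is not non-inferiority**

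Assumptions: SD 15, 20 or 22; iMBTSR truly 7 points worse, which is exactly at the margin; unadjusted two-sided 5% t-test of the two active arms. SE = SD × √(2/n), non-centrality = 7/SE, and the probability of a non-significant result is read from the non-central t distribution with 2n − 2 degrees of freedom.

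| n per arm | SD | SE | 7/SE | P(non-significant) |
|---|---|---|---|---|
| 14 | 15 | 5.67 | 1.23 | 0.78 |
| 14 | 20 | 7.56 | 0.93 | 0.86 |
| 14 | 22 | 8.31 | 0.84 | 0.87 |
| 18 | 15 | 5.00 | 1.40 | 0.73 |
| 18 | 20 | 6.67 | 1.05 | 0.82 |
| 18 | 22 | 7.33 | 0.95 | 0.85 |

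**4. The three-arm F-test behaves differently**

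Consider a one-way F-test on week-8 scores at 14 per arm, with iMBTSR 7 points worse than ICBT and ICBT an assumed 20 points better than the waiting list. The squared deviations of the means 0, 7 and 20 sum to 206, so the non-centrality is 14 × 206/SD²: 12.8, 7.2 and 6.0 for SD 15, 20 and 22. P(non-significant) is 0.12, 0.37 and 0.45. With an assumed 15-point advantage it is 0.38, 0.62 and 0.68. The omnibus result is therefore driven largely by the waiting list.

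**5. What the correct analysis would deliver at the planned size**

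The 90% CI half-width is t₀.₉₅ × SE. At 18 per arm with no dropout, t on 34 degrees of freedom is 1.691:

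- SD 15: 1.691 × 5.00 = 8.5
- SD 20: 1.691 × 6.67 = 11.3
- SD 22: 1.691 × 7.33 = 12.4

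All exceed 7, so an observed difference of zero would not meet the rule. Baseline adjustment narrows the interval. With an assumed baseline to week-8 correlation of 0.5 the factor is √(1 − 0.25) = 0.866, giving about 7.3, 9.8 and 10.7.

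**The case against.** The best defence is that the margin, the end point and week 8 are all in the article, under Sample size {14}, and that Objectives {7} plans to compare the two treatments with each other as well as with the waiting list. An article may leave the contrast and the decision rule to an analysis plan that is not shown. A week-8 contrast with a confidence interval can also be taken from a repeated-measures model. This stands in part: the model class is not itself the obstacle, and the repair is small. It does not remove the point. {20a} is not silent. It names a method for the primary outcome, and the test that this method supplies is not the one for which the sample size section plans.

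Four stronger readings are tempting but not supported.

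- A reader might infer that a null result will be reported as non-inferiority, with a false-claim rate near 80%. No section says so. The 73-87% figures are for a pairwise test at assumed SDs.
- A reader might infer that a non-significant ANOVA is the likely outcome. For the three-arm test this depends on the advantage over waiting, as step 4 shows.
- A reader might infer that the ANOVA pools all four THI occasions. {20a} does not say which occasions enter, and waiting-list participants move to a treatment after 8 weeks, so a pre/post analysis is a natural reading.
- A reader might see a shift of end point between the week-8 score and the outcomes section's "Change in the score from baseline will be assessed". Under randomisation, both estimate the same between-arm difference at week 8.

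The ANOVA sentence can also be read as covering all three arms, so it does not exclude the head-to-head comparison. It only fails to define it.

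**Conclusion.** The point holds as a mismatch within the article: a non-inferiority question with a stated end point and margin is paired with a test of no difference that does not use them. This rests on the text alone and on no assumed SD. It needs correcting before analysis, because without a margin-based rule the trial's main claim has no valid test.

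The numerical illustration has a limited purpose. It shows that absence of a pairwise difference cannot stand in for non-inferiority at 14 to 18 per arm. It assumes SDs of 15 to 22, an unadjusted comparison and a true difference of exactly 7 points, and it says nothing about the operating characteristics of the three-arm F-test.

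**What to change.** Replace the primary-outcome sentence in {20a} with a paragraph that states the following.

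- **Estimand and model:** the baseline-adjusted difference in week-8 THI, iMBTSR minus ICBT, from ANCOVA or as the week-8 contrast of a repeated-measures model. Higher THI is worse, so a positive value favours ICBT.
- **Decision rule:** conclude non-inferiority only if the upper confidence limit is below +7, at a stated one-sided alpha. The article does not say whether its 5% is one-sided or two-sided. If one-sided, use a 90% CI; if two-sided, a 95% CI.
- **Analysis sets:** require the rule to be met in both the per-protocol and the intention-to-treat sets already named in {20c}.
- **Waiting list:** treat comparisons with it as separate superiority tests.
- **Interpretation:** state that a non-significant ANOVA is not evidence of non-inferiority. The ANOVA may stay as a descriptive analysis.

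The wording costs one paragraph and uses the same data and software. According to Trial status, recruitment had not begun, so the change could precede any data. The real cost is candour about precision. With 90% CI half-widths of about 8.5 to 12.4 points before baseline adjustment at 18 per arm, the correct analysis may well be inconclusive. The protocol should acknowledge this and support its sample size with a stated SD.

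### The repeated-measures ANOVA named for THI does not fix which visits it contains; with all four in, it would discard observed week-8 values, and imputation is written only for the intention-to-treat comparison

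*Protocol article*

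**What the plan says.** The section on primary outcome measures schedules the outcome four times: "Assessment with THI will take place at pre-treatment, post-treatment at week 8, and 3 and 12 months post-treatment follow-ups". Sample size {14} fixes the test at one of them: "The primary end point used for the non-inferiority test was the THI score at 8 weeks", with a margin of 7 points.

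The section on statistical methods for primary and secondary outcomes {20a} names one model for group comparisons. To assess changes in the outcomes and compare them across arms, "repeated-measures ANOVAs will be performed". It does not list the visits in each model. It does separate effects "from the pre-test to the post-test for short-term effects and from the pre-test to follow-up for long-term effects", but that sentence concerns effect sizes.

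On analysis sets and missing data, section {20c} says: "The results will be calculated based on the per-protocol approach and will also be compared with those obtained using the intention-to-treat approach". For the intention-to-treat analysis it adds a missing value analysis, and then: "If necessary, missing data will be filled in using multiple imputation techniques". No imputation is stated for the per-protocol results.

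**The concern.** Classical repeated-measures ANOVA is a complete-case method over the visits it contains. A participant with baseline and week-8 THI but no month-12 value contributes nothing to a four-visit model, not even to its week-8 comparison. The primary question is answered at week 8, so a later missed visit should not remove a primary endpoint value already in hand.

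Two things are at stake. The first is precision, in a trial planned on 42 analysed participants. The second is validity: if those who leave after week 8 differ in week-8 THI, and differ in another way in the other arm, a completers-only contrast between iMBTSR and ICBT is distorted although the data to avoid this were collected.

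**Working it through.** **Inputs.** From Sample size {14}: 42 required in total, a 25% increase for dropout, about 18 per arm, margin 7, power 80%, alpha 5% (sidedness not stated). The article gives no SD, no dropout by visit and no dropout mechanism. Everything below that depends on these is assumed.

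**1. The plan's own figures.** 42 × 1.25 = 52.5; 52.5 / 3 = 17.5, rounded up to 18 per arm, or 54 in total. This reproduces. The 42 itself cannot be reproduced without an SD. Solving for the SD that gives 14 per arm with a true difference of 0, SD = 7 × √(14/2) / (z for 1 − alpha + z for 0.80):
- one-sided 0.05: 18.52 / (1.645 + 0.842) = 7.45
- one-sided 0.025: 18.52 / (1.960 + 0.842) = 6.61

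**2. Retention if all four visits enter and nothing is imputed.** Assume the whole 25% is lost by week 8, then a fraction l at each of the two follow-ups. With week-8 data: 54 × 0.75 = 40.5. Complete at all four: 40.5 × (1 − l)². At a constant SD, the confidence interval widens by √(40.5 / complete) = 1 / (1 − l).

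| l per follow-up | Complete cases | Per arm | CI width factor |
|---|---|---|---|
| 5% | 36.6 | 12.2 | 1.05 |
| 10% | 32.8 | 10.9 | 1.11 |
| 15% | 29.3 | 9.8 | 1.18 |

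**3. A second missingness pattern.** Start from 18 per arm, with a fraction m missing independently at each of three post-baseline visits. Week-8 observed is 18 × (1 − m); complete is 18 × (1 − m)³. Power uses the normal approximation at the back-solved SD of 7.45, one-sided 0.05.

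| m | Week-8 observed | Complete | Dropped although observed | Power, all week-8 vs complete |
|---|---|---|---|---|
| 5% | 17.1 | 15.4 | 1.7 | not computed |
| 10% | 16.2 | 13.1 | 3.1 | 0.85 vs 0.78 |
| 15% | 15.3 | 11.1 | 4.2 | 0.83 vs 0.71 |
| 25% | 13.5 | 7.6 | 5.9 | 0.79 vs 0.57 |

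With monotone dropout of 15/20/25% at week 8, month 3 and month 12, the figures are 15.3 against 13.5, a loss of 1.8 per arm. Across these patterns about 2 to 6 of 18 per arm are dropped despite an observed week-8 THI.

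**4. Bias.** This was simulated for two equally effective active arms of 18, with correlation 0.6 and later loss in one arm only rising with week-8 THI (log-odds 0.7–1.0 per SD). The contrast is a completers-only ANCOVA. Ranges cover the two log-odds values and repeated runs.

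| SD | Later loss | Bias, THI points |
|---|---|---|
| 18 | 25% | 1.8–2.9 |
| 18 | 10% | 0.8–1.1 |
| 7.45 | 25% | 0.8–1.0 |
| 7.45 | 10% | 0.3–0.5 |

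With all observed week-8 values, the bias at SD 18 and 25% loss is below 0.1. In the settings shown, the completers-only bias therefore runs from 0.3 / 7 = 4% to 2.9 / 7 = 41% of the margin.

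**5. Where the loss is zero.** With only baseline and week 8 in the ANOVA, a missed follow-up removes nobody. The same holds for an imputed intention-to-treat data set.

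**The case against.** The strongest reply is that the article never says four visits enter one model. It says ANOVAs, in the plural, and several features fit a baseline/week-8 model. The endpoint is at week 8. Short-term and long-term effect sizes are kept apart. The ANOVAs compare the interventions with a control group that, under Intervention description {11a}, moves to an active intervention after 8 weeks, so an untreated control exists only up to then. On that reading the loss and the bias are both zero. This stands: a reader might infer that the plan commits to a four-visit analysis, and the text does not support that.

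A reader might also infer that the whole analysis is complete-case. That is not supported either. Section {20c} foresees multiple imputation for intention-to-treat, and its conditional wording can be read as meaning whenever data are missing. In addition, section {18b} asks participants who discontinue to complete follow-up questionnaires. What this reply does not reach is the per-protocol result, which is named first and has no stated imputation.

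Finally, which visits enter a model is often left to an analysis plan, and an article condenses. Silence alone would be no finding. But the article does name a model, for a four-visit outcome with dropout expected, and under one permitted reading that model discards primary endpoint data.

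**Conclusion.** The point holds conditionally. The protocol names a complete-case method for THI without fixing its visits, and its only stated remedy for missing values is conditional and tied to the intention-to-treat comparison. If all four visits enter, observed week-8 values are lost from the per-protocol comparison. Under the assumed losses, about 37 to 29 complete cases remain against about 40, and the confidence interval is about 5–18% wider. The lower end is minor.

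A reader might take the larger simulated figures to mean that the non-inferiority contrast will be off by 2 to 3 points. The documents do not support that. Such a bias needs later dropout that depends on week-8 THI differently by arm, and its size rests on an SD and a loss rate the article does not give. With a smaller SD and less loss it falls below 1 point.

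This is a cheap improvement worth making, not a demonstrated error in the primary analysis.

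**What to change.** In section {20a}, replace the repeated-measures ANOVA with a linear mixed model for repeated measures on all observed THI values: baseline THI as covariate; arm, visit and arm-by-visit as fixed effects; unstructured covariance. Take the week-8 iMBTSR minus ICBT difference and its confidence interval from this model and compare the relevant limit with the 7-point margin. Keep multiple imputation as a sensitivity analysis.

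An ANCOVA of week-8 THI adjusted for baseline THI would remove this loss equally well and is simpler. If a baseline/week-8 model was always intended, saying so also closes the point.

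The cost is wording only: no further data or participants. The downside is a slightly more complex model at this sample size. The mixed model does not undo exclusions made by the per-protocol definition, which is a separate matter.
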